## Objectives

According to our preregistration (see below), objectives of the SMART-AGE trial are as follows: Can the regular use of the offered apps (1) prevent or reduce loneliness and promote social support (particularly smartVERNETZT), (2) improve motor capacity (particularly KOKU), (3) increase health self-awareness and health-related control beliefs (particularly smartIMPULS), and (4) increase technology-related skills and the acceptance of technology?

To address these objectives, we decided for an intervention scheme as follows: a full intervention group (IG), a partial IG, and an active control group (CG). An active CG was installed to ensure that observed effects can be attributed to app use and not simply to the provision of a tablet to the participants coming with some social attention. In the full intervention condition, the participants will have access to all of the SMART-AGE specific apps, namely smartVERNETZT, KOKU, smartIMPULS, and smartFEEDBACK. In the partial intervention condition, the participants will have access to two SMART-AGE specific apps, namely smartVERNETZT (containing all standard apps) and smartFEEDBACK. This arm allows us to investigate the impact of the smartVERNETZT app without the co-use of other apps that also aim to improve the quality of life. It also serves as a most direct comparison to the previous PRISM trial [6]. Participants in the active CG will just be given the device and receive a basic introduction to publicly available and pre-installed standard apps (e.g., calendar app, e-mail app). In all of the three treatment arms, participants will receive a tablet and be given a short introduction on how to use a tablet in general.

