Hypotheses based on these treatment variations are as follows:Participants who use a tablet equipped with the smartVERNETZT app (full and partial IG), which encourages social networking and participation, are expected to experience lower levels of loneliness and higher levels of social engagement compared to those using a tablet with only standard applications. This effect is expected to be even larger in the full IG than in the partial IG due to the synergistic benefits derived from using all apps designed to enhance quality of life.Participants who are in the full IG (who all have access to smartIMPULS) have increased health-related self-awareness and health-related control beliefs, compared to the active control and the partial IG, who both do not have access to smartIMPULS. Between the latter two groups, we do not expect any differences in health-related self-awareness and health-related control beliefs.Participants who are in the full IG (who all have access to KOKU) will show better gait performance and motor functioning, compared to the active control and the partial IG, who both do not have access to KOKU. Between the latter two groups, we do not expect any differences in gait performance and motor functioning.Over time, participants using a tablet will report greater technology acceptance and develop technology-related skills than before using a tablet. This increase in technology acceptance and technology-related skills is larger for participants in the full and partial IG. In addition, exploratory analysis will give more insight into the dose–response relationship between the amount of apps and their impact on technology acceptance and technology-related skills***.***

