### Participant timeline

Home-based assessments take place at the time of study enrollment (T1) and after 6 months (T6). In addition, a brief online self-assessment will be conducted 3 months after study enrollment (T3). At the beginning of the first home visit (HV; day 1 in T1), participants are informed about data protection, can ask open questions, and get general information about the study. Then they are provided with a tablet, a corresponding manual, and are instructed on how to use the tablet in a short training session. At that moment, the tablet is switched to “study mode,” enabling the monitoring of app usage data of the participants from that point forward. Afterwards the online-assessments are explained and set up on the tablet. Then the home-based assessments take place including cognitive and motoric measurements. During the motor capacity assessment, the body-fixed movement sensor is placed on the participant’s lower back.

One week after the initial HV, the randomization has already taken place, and a second HV is conducted for participants of all groups. During this visit, the tablets are modified allowing participants in both IGs (arms 1 and 2) access to two SMART-AGE specific apps: smartVERNETZT and smartFEEDBACK. These groups also receive instructions and a manual on how to use these new apps. Participants in the CG (arm 3) are given access to the standard applications on the tablet. However, detailed explanations are only given for the video chat tool. The documents containing information about the SPs, completed and signed during the HVs, as well as the data sheets of the cognitive test battery, are securely stored in a locked cabinet in SMART-AGE designated office spaces. Four to 6 weeks after the second HV, participants in the full IG additionally receive access to and are instructed in the use of the KOKU app. Approximately 10 days after the digital assessment at 3 months, the participants of the full IG are introduced to the smartIMPULS app during HV IV.

In order to counterbalance potential social activation effects, 25% of participants in study arms 2 and 3 (active CG and the partial IG) were randomly selected to receive one additional video calls. Randomization was performed using the R package “blockrand” [39].

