### Eligibility criteria

Interested individuals who contact the study team undergo a screening process over a phone call to determine if they meet specific criteria for inclusion or exclusion from the study. Individuals who are younger than 67 or living in a nursing home, have severe cognitive limitations, no internet access, no PC/Tablet experience, severe medical conditions, severe visual/hearing impairments, no/poor knowledge of German, or work 20 + hours per week are excluded.

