## Methods: data collection, management, and analysis

### Data collection methods

At each of these two time points (T1 and T6), trained researchers will visit participants at home and conduct a number of assessments (see Appendix–A2), including a battery of cognitive tasks and the application of state-of-the-art body-fixed movement sensors (Axivity AX6, Axivity Ltd, Newcastle upon Tyne) to measure physical activity for 7 consecutive days. Moreover, participants will be asked to complete a set of web-based questionnaires using their tablet within a week of each of these visits by means of a RedCap data architecture. Web-based questionnaires are sorted into four sets of comparable length that each take no longer than an hour to complete. Participants will be asked to respond to one set of questionnaires per day. After the second and fourth set of questions, participants perform further cognitive tasks on the tablet. The first set of questions, presented on the first day, includes the primary outcome measures and is repeated at T3 in order to have a higher granularity of primary outcome data.

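### Hypothesis 4 compares technology acceptance and skills with the state before tablet use, but the described baseline follows tablet handover and training, and no arm is tablet-free

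*Protocol article*

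**What the plan says.** Hypothesis 4 (Protocol article, Objectives) has two directional parts. The first is a before-after statement: "Over time, participants using a tablet will report greater technology acceptance and develop technology-related skills than before using a tablet". The second is a comparison of arms: "This increase in technology acceptance and technology-related skills is larger for participants in the full and partial IG". Only a further dose-response analysis is labelled exploratory, so both parts read as confirmatory. Technology acceptance, competence and usage is one of the four primary outcome domains (Outcomes).

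Participant timeline gives the order of events at the first home visit. After the information and questions, "Then they are provided with a tablet, a corresponding manual, and are instructed on how to use the tablet in a short training session". Then: "Afterwards the online-assessments are explained and set up on the tablet". Data collection methods adds that "participants will be asked to complete a set of web-based questionnaires using their tablet within a week of each of these visits". It also says of the primary measures: "The first set of questions, presented on the first day, includes the primary outcome measures and is repeated at T3".

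On comparators, Objectives states: "In all of the three treatment arms, participants will receive a tablet". It explains that the control arm is given a device so that differences can be credited to the apps and not to being handed a tablet. Among the reasons for exclusion, Eligibility criteria lists "no internet access, no PC/Tablet experience". Statistical methods models time with three levels: study start, month 3 and month 6.

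**The concern.** A before-after claim about tablet use needs a measurement taken before tablet use. To credit the change to the tablet, it also needs people who did not get one. The document describes neither. Its first measurement comes after handover and a short training session and is made on the device itself. Constructs such as computer anxiety and user frustration could already shift at that first contact.

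At stake is how the time effect in the 3 × 3 model is read for a primary domain. Set against the first sentence of Hypothesis 4, a significant overall rise could be taken to show that tablet use improves acceptance and skills, and a flat result could be taken to show that it does not. Neither conclusion would follow. A rise may come from retesting, calendar time or use of other devices. A flat course may mean that early gains were already in the T1 value.

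**Working it through.** **Step 1: claim against schedule.**
- Reference state named in Hypothesis 4: before using a tablet.
- Order at T1: tablet, manual and training; then set-up of the online assessments on the tablet; then the questionnaires, answered on the tablet within a week of the visit.
- Time points in the model: T1, T3 and T6. None is described as preceding handover.

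The change that can be estimated is therefore (T3 or T6) minus (shortly after introduction), not minus (before tablet).

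**Step 2: comparator.** Every arm has the tablet and the introduction. Schematically, the mean change in each arm is
- active control: post-T1 tablet effect + drift;
- intervention group: post-T1 tablet effect + drift + app effect.

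The difference between arms leaves the app effect. The tablet effect and the drift always appear together, and no contrast in the design separates them.

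**Step 3: the planned sample size, used as an input below.** From Sample size: 128 parameters × 5 = 640. Allowing for 10% dropout, 640/0.90 = 711.1, so 712. The next multiple of 72 is 720, which reproduces the planned figure. The stated power above 0.99 also reproduces (about 1.00), but it concerns rejecting a badly fitting model, not detecting a mean change.

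**Step 4: how small a drift would be significant.** Assumptions, which are not in the document: 648 completers (720 × 0.90), a simple two-sided test of the pooled T1-T6 change at 0.05, and drift expressed in SD of the change score.

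Detectable change at 80% power: (1.960 + 0.842)/√648 = 2.802/25.46 = 0.11 SD.

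Probability that pure drift δ is significant: Φ(δ√648 − 1.960).
- δ = 0.10: Φ(2.546 − 1.960) = 0.72
- δ = 0.15: Φ(3.818 − 1.960) = 0.97
- δ = 0.20: Φ(5.091 − 1.960) = 0.999

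With all 720 analysed, the first two become 0.77 and 0.98.

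**Step 5: what the randomised contrasts can detect, on the same assumptions (216 per arm).**
- One arm against another: 2.802 × √(2/216) = 0.27 SD.
- Both intervention groups against control: 2.802 × √(1/216 + 1/432) = 0.23 SD.

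These contrasts are free of common drift. The pooled time effect is the most sensitive of these tests and the only one open to drift.

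**The case against.** The case for leaving the text alone has real force. The sentence predicts change over time. It does not say that the tablet causes the change or promise a comparison with tablet-free people. Change across T1, T3 and T6 is estimable, and nothing in the document says that a time effect will be presented as a tablet effect. The authors clearly understand the role of an active control, and Statistical methods already plans contrasts of both intervention groups with control and of full with partial intervention. Gains absorbed into T1, taken alone, would work against the hypothesis. The hypotheses were preregistered, and recruitment ended on 31 August 2024, so deleting a clause now would itself be a departure.

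Most of this stands and limits the point. What remains is that the sentence names a reference state for which no measurement is described, in a primary domain and without an exploratory label.

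A reader might infer stronger versions that the documents do not support:
- **That a week of tablet use precedes baseline.** The primary measures are in the first questionnaire set, on the first day of the series. A week is an upper bound, and exposure may be little more than the training session.
- **That a known or large share of the gain is absorbed.** The document gives no figure and calls the session short. Manuals, videos and a helpline support learning afterwards.
- **That participants were already tablet users.** The criterion combines PC and tablet, so PC users new to tablets are eligible, and the phrase fits them.

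**Conclusion.** The point holds in a limited form. As described, the plan has no pre-tablet technology measurement and no tablet-free comparator. The overall time effect is therefore uncontrolled change since shortly after tablet introduction. It may miss early gains by an unknown amount. A drift of 0.10 to 0.20 SD would be significant with probability from about 0.72 to above 0.99, under the assumptions of 648 completers, a two-sided 0.05 test and drift in units of the change-score SD.

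It would be too strong to say that Hypothesis 4 is untestable. Its second sentence is tested by randomised comparison, and the change since T1 is a legitimate descriptive quantity. One reservation remains: the full list of assessments is in an appendix that is not shown. A technology measure taken before handover is possible, though nothing in the text indicates one. It would supply the missing reference measurement but not the missing comparator.

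No sample size or randomised contrast changes. What changes is the conclusion that the trial may draw from the time effect on one primary domain, so this should be settled before results are interpreted.

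**What to change.** In Hypothesis 4 and in Statistical methods:

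1. State that the planned arm-by-time contrasts (full and partial intervention group versus active control) carry the confirmatory claim for technology acceptance and skills.
2. Report the all-arm time effect as descriptive change since T1, noting that T1 follows tablet introduction, and do not attribute it to the tablet.
3. Record both as a dated clarification of the preregistered hypothesis, leaving the registered wording visible.
4. If the appendix does contain a technology measure taken before handover, say so and use it as the reference for the descriptive change.

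A breakdown by earlier tablet use should not be promised unless it was recorded separately from PC use, since only a combined criterion is shown.

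The cost is one sentence in the hypothesis and one line in the methods, with no new data. The sponsor gives up one uncontrolled confirmatory claim.

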## Method: participants, interventions, and outcomes

### Trial design

The study is a three-armed, randomized controlled trial with repeated measures over 6 months. Treatment relies on an android-based tablet computer, on which three apps offering structured interventions in the three core areas of social participation, physical fitness, and health awareness are pre-installed. Also, an app designed to provide study participants with a structured feedback option at any time of the trial is offered. Participants are randomly assigned to three intervention arms and assessed at baseline and after 3 and 6 months. Arm 1 receives the full intervention, consisting of the social participation app, the physical fitness app, the health awareness app, and the feedback app. The health awareness app is available in months 4 to 6, meaning that participants receive the full three-app intervention only in the second half of the intervention period. Arm 2 receives the social participation app and the feedback app throughout the intervention. Arm 3 serves as an active control condition in that solely a stand-alone tablet implementation with a low-dose introduction to publicly available standard apps are provided. The trial protocol follows the Standard Protocol Items: Recommendations for Interventional Trials (SPIRIT) [38]. A completed SPIRIT checklist is provided in the Additional file. A detailed overview of the study procedure is provided in Fig. 2.

**Fig. 2 Fig2:**
[figure not shown]
Overview of SMART-AGE design. Note:* N* = total sample size, *n* = sample size in the treatment arms, CT = cognitive tasks, T1/T3/T6 = time point in study

### Participant timeline

Home-based assessments take place at the time of study enrollment (T1) and after 6 months (T6). In addition, a brief online self-assessment will be conducted 3 months after study enrollment (T3). At the beginning of the first home visit (HV; day 1 in T1), participants are informed about data protection, can ask open questions, and get general information about the study. Then they are provided with a tablet, a corresponding manual, and are instructed on how to use the tablet in a short training session. At that moment, the tablet is switched to “study mode,” enabling the monitoring of app usage data of the participants from that point forward. Afterwards the online-assessments are explained and set up on the tablet. Then the home-based assessments take place including cognitive and motoric measurements. During the motor capacity assessment, the body-fixed movement sensor is placed on the participant’s lower back.

One week after the initial HV, the randomization has already taken place, and a second HV is conducted for participants of all groups. During this visit, the tablets are modified allowing participants in both IGs (arms 1 and 2) access to two SMART-AGE specific apps: smartVERNETZT and smartFEEDBACK. These groups also receive instructions and a manual on how to use these new apps. Participants in the CG (arm 3) are given access to the standard applications on the tablet. However, detailed explanations are only given for the video chat tool. The documents containing information about the SPs, completed and signed during the HVs, as well as the data sheets of the cognitive test battery, are securely stored in a locked cabinet in SMART-AGE designated office spaces. Four to 6 weeks after the second HV, participants in the full IG additionally receive access to and are instructed in the use of the KOKU app. Approximately 10 days after the digital assessment at 3 months, the participants of the full IG are introduced to the smartIMPULS app during HV IV.

In order to counterbalance potential social activation effects, 25% of participants in study arms 2 and 3 (active CG and the partial IG) were randomly selected to receive one additional video calls. Randomization was performed using the R package “blockrand” [39].

Finally, it deserves mentioning that intervention schemes are implemented without altering usual care pathways, which will continue without any change in both trial arms. There are no restrictions regarding concomitant care provision or change during the trial.

For a full overview of SMART-AGE trial components, see checklist of SPIRIT provided in Fig. 3.

**Fig. 3 Fig3:**
[figure not shown]
Standard Protocol Items: Recommendations for Interventional Trials (SPIRIT) figure (numbers indicated under the heading “time points” represent month)

### Trial setting

The SMART-AGE trial addresses community-dwelling older adults in the cities of Heidelberg and Mannheim (Germany). Cities were selected due to their nearness to the university’s study site and socio-structural differences. Heidelberg is a since long-time established university city with overall relatively high socio-economic level, limited within-community heterogeneity, and low migration rate. In some contrast, Mannheim comes with overall relatively lower socio-economic level, pronounced within-community heterogeneity, and high migration rate.

### Eligibility criteria

Interested individuals who contact the study team undergo a screening process over a phone call to determine if they meet specific criteria for inclusion or exclusion from the study. Individuals who are younger than 67 or living in a nursing home, have severe cognitive limitations, no internet access, no PC/Tablet experience, severe medical conditions, severe visual/hearing impairments, no/poor knowledge of German, or work 20 + hours per week are excluded.

### Intervention

SMART-AGE’s digital intervention builds to a large extent on previously successfully evaluated tools [6, 40]. In this context, smartVERNETZT represents the German adaptation and further development of the successfully tested PRISM system [6]. The app KOKU also underwent intensive testing within British public health improvement efforts [26, 40]. The app smartIMPULS represents the translation of an earlier system completely focusing on geriatric patients to healthy older adults (project: SINQ-Service integration and network management to improve social coexistence of geriatric patients in the community [41]). All apps underwent in SMART-AGE additional testing to assess their usability and feasibility. Focus group interviews with nine participants who used smartVERNETZT and smartFEEDBACK for at least 7 days indicated that the app was perceived as engaging and user-friendly [42]. Internal pilot testing of KOKU confirmed previous findings [26], suggesting that the app was perceived as easy to use, useful and enjoyable. Given the new development of smartIMPULS based on an earlier geriatric patient version, a 6-week pilot study with 30 participants was conducted, in which the system achieved a score of approximately 77 in the System Usability Scale [43], which indicates good usability [44]. Based on feedback in pre-studies, the user surface and content of the apps were further optimized.

The programming of the apps smartVERNETZT, smartIMPULS, and smartFEEDBACK was conducted by the Institute of Computer Science at the University of Heidelberg. The apps are accessed via a tablet (Lenovo M10 FHD Plus). Studies indicate that tablets are well-accepted by older individuals due to their intuitive gesture control and convenient size [45].

The usage of the apps is monitored, and in case of 2 weeks of non-use, a single reminder email is sent to the tablet. In addition to digital and analog user manuals and instructional videos, a helpline (via email and phone) has been established. For details on data privacy and security measures related to the apps, please refer to the section “Data storage, data processing, and data quality.” Images of the apps are provided in the supplement (see Appendix-A1). Table 1 provides an overview of the contents of apps used.

**Table 1 Tab1:** Overview of Contents of Apps Used in SMART-AGE

Name of app	App feature/content
smartVERNETZT	– Weekly news on findings on physical activity, technology, social participation and local events – Integrated tools: calendar, address book, camera, notes, clock, calculator, Internet browser and games are included – Provides links to health websites, local counseling services, digital literacy resources, cognitive attention games, analog exercise programs, activities and offers (e.g., group meetings, volunteering), and local educational programs – Allows social networking through e-mail, social networks, and video chat
KOKU	– Progressively structuredtraining program comprising seven levels, each lasting a minimum of 2 weeks. Each week includes 3 training days, with three exercises per day; Green check marks indicate progress – Gamified training with an interactive avatar, demonstrating 26 strength and balance exercises (with goals description and safety instructions), based on evidence-based fall-prevention programs (Otago, FaME [46, 47]) – Users provide feedback on physical exertion; based on this training progression is automatically adjusted – Four health literacy games on home safety, bone health, nutrition and hydration
smartIMPULS	– Daily prompts with one to four questions addressing current life, functioning in daily life tasks and health situations – Addresses the following health domains: nutrition, activities of daily living, mobility, social participation, cognitive functioning, physical functioning, psychological factors, preventive health check-ups, pain, fear of falling, perceived stress, hearing ability, and vision – Questions repeat at set intervals based on expected changes in each domain; unanswered questions accumulate but can be skipped – Supports attention to specific health domains by giving hints based on user responses – Hints suggest follow-up actions (e.g., doctor visit, counseling) or offer additional information – Provides an overview of given answers, filterable by health domains and received hints, including status indicators (new, postponed, completed)
smartFEEDBACK	– Allows users to provide feedback on app use and usability issues at any time – Supports both explicit and implicit feedback, either voluntarily submitted (push) or prompted by the system (pull) – Up to five feedback questions per day (pull); all questions can be skipped

